We are conducting a population-based, pragmatic cluster-randomized clinical trial to implement and evaluate a direct-to-family, virtual, personalized, family-centered communication and decision-making tool - the Family Genetic Health Program (FGHP) - to close the gap in GRE and inform prevention and early detection strategies for relatives of patients with HCS. We use a unique Surveillance, Epidemiology, and End Results (SEER)-based data infrastructure that we pioneered to identify patients diagnosed with cancer in the states of Georgia and California who carry a PV in any clinically tested cancer susceptibility gene [14–16]. We target patients approximately three years after diagnosis in order to leverage our data infrastructure to: (1) identify a large, clinically and socially diverse cancer registry-based cohort of patients who tested positive for a clinically relevant germline PV; (2) use mature linked vital statistics data to identify patients alive ahead of our initial contact; and (3) use the Initiative data infrastructure to efficiently identify the gene(s) in which a PV is linked to the patient. We engage a clinically and socially diverse patient cohort with HCS and their family members using our virtual communication and decision-making approach, including an offer of clinical genetic testing and results reporting to first- and second-degree relatives, in partnership with a commercial laboratory (Color Health, Inc.) that has extensive experience with internet-based testing strategies in the US. This publication represents the documentation just prior the close of enrollment of the final protocol as carried out in the execution of the study. Where there are any important changes in execution of the protocol from the version submitted to our IRB dated 10/28/2022 (**see supplemental material**) we have noted them and discussed their potential impact in the text.

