### Primary Aim

**To determine the independent effects of the two virtual platform design features on relatives’ receipt of genetic testing.** We hypothesize that increased genetic risk navigation support and the availability of lower cost testing will increase the proportion of first- and second-degree relatives reported by patients on baseline survey who complete genetic testing through the study platform (primary outcome).

### Secondary aim 1

To determine the independent effects of the two virtual platform design features on the proportion of relatives invited by each patient to enroll in the study. We hypothesize that increased genetic risk navigation support and the availability of lower-cost testing will increase the proportion of first- and second-degree relatives reported by patients on a baseline survey who are invited by the patients to initiate GRE through the study platform (secondary outcome).

### Secondary aim 2

To determine the independent effects of the two virtual platform design features on cancer patients’ assessment of communication with their relatives about hereditary cancer and genetic risk evaluation. We hypothesize that increased genetic risk navigation support and the availability of lower-cost testing will substantially improve cancer patients’ assessment of their communication with relatives about hereditary cancer and genetic risk evaluation (secondary outcome).

### Secondary aim 3

To determine the independent effects of the two virtual platform design features on relatives’ receipt of a formal cancer genetic counseling session in practice. We hypothesize that increased genetic risk navigation support and the availability of lower-cost testing will increase the proportion of relatives enrolled in the trial that complete formal genetic risk evaluation with a clinician, after GIFT study participation.

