## Relatives

For the relative-level intervention, relatives first complete a brief eligibility screener. Eligible relatives are guided through an electronic baseline survey to collect information needed to tailor their intervention experience and are then given access to the online GIFT Study website. It is available to them for a total of six months, and they can access it as many times, and for as much time, as they want.

The study website guides relatives through the use of the intervention platform. Each feature is presented and the relative is able to choose how deeply to engage with each one. Features available to relatives in all four Study Arms include:

Key facts and education about genetics and how it relates to cancer risk, the different types of genetic test results and their meaning, and privacy regarding genetic test results.

An exercise designed to help them consider their reasons for getting genetic testing (including commonly endorsed motivational statements and commonly endorsed hesitation statements). Motivational testimonials accompany this section to gently steer the reader in the direction of getting tested (which is clinically appropriate in this set of families with hereditary cancer syndromes).

A brief description of the Color Health genetic testing process and the ability to follow a unique link to order free ($0) or low-cost ($50) genetic testing from Color (according to their Study Arm) (first 90 days only).

The ability to consent to share the fact that they have enrolled in the study with the patient who invited them to join.

The study website contains a unique link to the Color website that embeds a unique Color alphanumeric token directly in the URL. This token allows Color to know how much to charge the relative participant for their genetic test ($50 vs. free) and that they are enrolled in the GIFT Study. No study participant PHI or PII is shared with Color using this token method. Relatives who click the link to order genetic testing follow Color’s standard procedures for ordering a genetic test, which includes informed consent for the testing procedure.

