### Navigator services

Relatives randomized by family to Study Arms 3 and 4 have access to the Family Health Navigator, via phone/email/ videoconference, who can help them use the website, answer questions, and order genetic testing via Color. In addition to responding to requests for help from relatives, the Navigator can also follow up with relatives in Arms 3 and 4 proactively to encourage them to complete study tasks (e.g., complete their baseline survey; consider clicking the link to go to Color’s website to learn more about genetic testing).

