**Secondary Aim 3**: To determine the independent effects of the two virtual platform design features on relatives’ receipt of a formal cancer genetic counseling session in practice. We hypothesize that increased genetic risk navigation support and the availability of lower cost testing will increase the proportion of relatives enrolled in the trial that complete formal genetic risk evaluation in their medical practice within six months after enrollment.	**Relative Receipt of Formal Genetic Risk Evaluation** Single survey question (mark all that apply) with 3 potential responses. “Yes, Color” and “Yes, outside of Color” will indicate receipt of formal GRE. See Appendix F for details. Assessed in the Relative Six-Month Follow-Up Survey	This is an important relative-centered outcomes that will illuminate improvements to our next generation initiatives.

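### Secondary Aim 3 hypothesizes evaluation in the relative's own medical practice, but its endpoint also counts a Color response, so a positive result could not show evaluation in practice.

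*Protocol article*

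**What the plan says.** Both the Objectives section and Table 4 give the objective of Secondary Aim 3 as the effect of the two design features on "relatives’ receipt of a formal cancer genetic counseling session in practice". The hypothesis then appears in two forms:

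- Table 4: enrolled relatives will "complete formal genetic risk evaluation in their medical practice within six months after enrollment".
- Objectives, Secondary aim 3: enrolled relatives will "complete formal genetic risk evaluation with a clinician, after GIFT study participation".

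The endpoint in Table 4 is a survey item in the relatives' six-month follow-up: "Single survey question (mark all that apply) with 3 potential responses". The scoring rule is "Yes, Color” and “Yes, outside of Color” will indicate receipt of formal GRE". The item's wording is referred to Appendix F, which is not shown.

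On Color itself, the Background names it as the commercial laboratory partner. The Relatives section gives every enrolled relative "the ability to follow a unique link to order free ($0) or low-cost ($50) genetic testing from Color (according to their Study Arm"). In Arms 3 and 4 relatives also have a Navigator "who can help them use the website, answer questions, and order genetic testing via Color".

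**The concern.** Within one row of Table 4, the hypothesis names the relative's medical practice as the setting and the scoring rule accepts a response tied to the study's own test vendor. Both randomized features act directly on use of that vendor: one sets the price of the Color test, the other supplies help in ordering it. A rise in Color responses is therefore a plausible direct result of randomization, whether or not any relative goes on to evaluation elsewhere.

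The Objectives section says the study should prepare relatives to engage their own clinicians. Among the primary and secondary outcomes, Aim 3 is the one that looks past the platform to that step. If its endpoint can turn positive without any change outside Color, a reader who takes the Table 4 hypothesis at face value will draw a conclusion that the endpoint does not measure.

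**Working it through.** **Step 1. Would a relative evaluated only through Color count?**

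| Text | Color-only evaluation counts? |
|---|---|
| Objective (Objectives section and Table 4) | Unclear; the phrase about practice can be read either way |
| Hypothesis, Table 4 | No; it specifies the relative's medical practice |
| Hypothesis, Objectives section | Possibly; a Color clinician would be a clinician |
| Endpoint scoring rule, Table 4 | Yes, explicitly |

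The clear conflict is between the second and fourth rows. The two hypotheses also differ from each other on setting and on timing (after participation, or within six months of enrollment).

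**Step 2. Is there a figure in the plan to reproduce?** The article gives no event rate, effect size or power for Aim 3. Only its expected denominator can be checked. With 412 patients and three relatives each (Relatives trial recruitment), 412 × 3 = 1236; at 30% enrollment, 1236 × 0.30 = 370.8, which agrees with the stated 371.

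**Step 3. Shift in the endpoint with no change outside Color.** All rates here are assumed. Let c be the proportion giving the Color response and q the proportion giving the outside-Color response, with q the same in both groups. A relative who marks both counts once. If the two responses are independent:

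- composite = 1 − (1 − q)(1 − c)
- difference = (1 − q)(c₁ − c₀)

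Suppose Color testing among enrolled relatives is 50% in one group and 65% in the other, and half of those tested report a Color session. Then c₀ = 0.50 × 0.5 = 0.25, c₁ = 0.65 × 0.5 = 0.325 and c₁ − c₀ = 0.075.

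- q = 0%: 0.075 × 1.00 = 7.5 points
- q = 10%: 0.075 × 0.90 = 6.75 points
- q = 20%: 0.075 × 0.80 = 6.0 points

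The 7.5 points is the upper bound for these inputs. If the extra Color responders tended also to report outside evaluation, the shift could fall below 6.

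**Step 4. Could such a shift reach significance?** This uses the same formula over a grid of assumed Color-response rates. The 371 relatives are split evenly over one factor (185.5 per level), the test is two-sided at 0.05, and clustering is ignored. Each cell gives the composite difference in points and the chance of a significant result. The true outside-Color effect is zero throughout.

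| Color response | q = 5% | q = 10% | q = 20% |
|---|---|---|---|
| 10% to 15% | 4.75; 23% | 4.5; 18% | 4.0; 13% |
| 10% to 20% | 9.5; 64% | 9.0; 53% | 8.0; 38% |
| 20% to 30% | 9.5; 52% | 9.0; 46% | 8.0; 35% |
| 30% to 45% | 14.25; 80% | 13.5; 75% | 12.0; 64% |

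Allowing for clustering within families would lower these chances. It would not remove the shift.

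**The case against.** The strongest reply has four parts.

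First, the conflict is narrow. Only the Table 4 hypothesis clearly excludes Color. The wording in the Objectives section could include a Color clinician, and the reference to practice in the objective is not decisive, since Table 4 uses the same phrase to justify a primary outcome that consists of Color testing. This stands: it would be wrong to say that the aim and both hypotheses all contradict the endpoint.

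Second, Appendix F is not shown and the article does not describe any counseling by Color. Reading the Color response as a session with Color is an inference from the response label and the aim. This also stands, although on any reading the response is tied to Color and not to the relative's own practice.

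Third, a reader might infer that Aim 3 merely repeats the primary outcome. The documents do not support that. The primary outcome is a test result in Color's quarterly report, over all relatives reported at baseline; Aim 3 is self-reported evaluation among enrolled relatives. Source, event and denominator differ. What remains is that both can move through the same channel.

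Fourth, a reader might infer that the endpoint is the error and must be cut back to the outside-Color response. Nothing in the article shows whether the endpoint or the aim's wording is wrong. The endpoint is explicit and pre-specified, and replacing it as enrollment closes is debatable. The two responses are recorded separately, so careful reporting could prevent misreading. That does not settle the matter, because the scoring rule as stated is the composite and the Table 4 hypothesis attached to it concerns own practice.

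**Conclusion.** The point holds as an inconsistency in the stated claim of a secondary aim. The Table 4 hypothesis and its scoring rule do not describe the same event, and the Objectives section offers a third version. Under the rule as written, Aim 3 can be positive with no change in evaluation outside Color, so it cannot by itself support a conclusion about the relative's own practice. The illustrative size is about 6 to 7.5 points, assuming Color testing of 50% and 65%, half of those tested reporting a Color session, and independent responses with outside-Color evaluation at 20% to 0%. None of these rates is in the document. It cannot be said from the article that the trial will reach a false conclusion, or that the composite is an illegitimate outcome.

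**What to change.** Before outcome analysis, and without sight of results by arm, reconcile the aim, both hypothesis wordings and the endpoint in one of two ways:

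1. Keep the pre-specified composite, and reword the aim and both hypotheses to formal evaluation from any source.
2. Score the aim on the outside-Color response, with the composite as a supportive outcome.

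Under either option, estimate the effect of each randomized factor on the outside-Color response and on the Color response separately. Base any statement about evaluation in practice on the outside-Color component alone. State one time window for the outcome.

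The first option costs a change of wording. The second redefines a pre-specified secondary outcome late in the trial, so it needs a dated and justified amendment. The item allows more than one response, so no new data are needed. The outside-Color component will have a lower event rate and a less precise estimate, and this should be said when it is reported.

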**Exploratory Aims**		
To explore the effect of the two virtual platform design features on the primary and secondary relatives testing outcomes described above across patient SES subgroups.	Family Genetic Testing Fraction and Family Invite Fraction – SES subgroup analyses. No new endpoints.	This is an important assessment of SES gradients in key outcomes across Trial arms that will inform whether there were disparities in the impact of the trial among patients and relatives.

**Other measures**: age, gender, education (from baseline cohort survey) census poverty level (from SEER)

### Data monitoring and collection

#### Patient and relative reported data

Data collected directly from patients and relatives (self-report survey data; patient-provided genetic testing results reports; relative contact information) is collected and stored online and initially managed by the University of Michigan Center for Health Communications Research (CHCR). The patient inception cohort have the option of completing the PIC survey via paper, which SEER study staff mail to a third-party data entry vendor (DataForce) for data entry. DataForce transfers the patient inception cohort survey data to CHCR via secure data transfer. The study website automatically records and saves relevant platform paradata (e.g., login, time spent per page, video watch counts). All personally identifiable information (PII) is stored in a separate file (linked to the participant’s unique Study ID), encrypted and password-protected, in order to manage study protocol adherence.

Study staff at the University of Michigan need access to the participant data stored by CHCR. All data is available via a password-protected project Dashboard Console built and administered by CHCR team members. Enrollment and study progress can be viewed directly on the console, and more detailed data files are available for download from the site as.csv files.

The Project Dashboard Console contains the following data elements and functionality:

Enrollment flow.Protocol adherence (e.g., module completion; patient outreach to relatives; relative initiation of genetic testing).Survey status.Participant contact information (if outreach or additional reminders needed).

The study team may request data that goes beyond what is available on the Dashboard Console; any files generated in response to such a request is shared with the study team via Dropbox, a secure collaborative storage system that is approved for PHI by the University of Michigan Health System. The UM study team has access to project data through the Project Dashboard Console. The Data Manager works with [name] and the CHCR staff to maintain the highest quality datasets. All datasets include the participants’ unique Access Code (Study ID), allowing linkage of all datasets on an ongoing basis. The linking file is kept in an encrypted and password protected file, stored on a secure server at UM and accessible only to the study team.

#### Administrative, electronic and registry data

Other study data is obtained via linkage with external sources, including: (1) clinical, genetic test results, and demographic data from the Georgia California Genetic Testing Linkage Initiative (IMS), and (2) genetic testing information from Color Health for relatives who opt to receive genetic testing via the FGHP (limited to whether testing was processed and completed). Data use agreements, Health Insurance Portability and Accountability Act (HIPAA) authorizations, and Institutional Review Board (IRB) approvals are established as required to use these data for research purposes and participant consent is obtained before any linkage occurs. A third-party honest broker (IMS) links these datasets and create the analytic datasets. All data sets shared with CHCR contain only the unique Study IDs. Any other patient identifiers are not included.

All patient data, including survey, FGHP, and registry data, are combined using the unique Study IDs to create a patient level analytic dataset. Data for relatives is similarly combined to create a relative level analytic dataset. These datasets are stored and maintained by the project analytic and data management team on the University of Michigan enterprise cloud storage as the location for all databases. Analytic datasets are dynamically generated from raw de-identified data files using a shared code base that is curated by the study data management team and stored and updated centrally, ensuring that all analyses across projects are based on up-to-date data and coding conventions. Dropbox version control allows reinstating prior versions to ensure reproducibility of earlier results.

#### Data storage and management

All study data is collected and stored by CHCR at the University of Michigan, including the merged analytic datasets and their component data sources. CHCR maintains a philosophical and programmatic commitment to propagating the findings and products of our research. CHCR has an extensive history of supporting the sharing of research data from the perspective of fortifying the principles of scientific inquiry, facilitating alternative examinations of research questions, and avoiding duplicative data collection efforts. This study’s Leadership Team ensures that data sharing is undertaken with attention to human subjects protections, respect for proprietary data, and maintaining integrity of the source data.

To ensure that the data are protected, CHCR uses virtualized servers provided by Michigan Medicine’s Health Information Technology & Services (HITS). This Virtualization Service provides safer retention of data through storage and backup, physical security reducing the risk of damage or theft, and meets the regulatory requirements needed for this environment.

All servers and the back-end databases are password protected. The server runs the Red Hat Enterprise Linux operating system and security patches and updates are downloaded and installed regularly. Each server is also protected by firewalls to restrict network access to the server. When a participant accesses the study website, content is transmitted securely using secure socket layer (SSL) protocol, the same protocol used to protect financial and other personal information when transmitted from a web site to a user’s browser. This prevents anyone else on the network from intercepting and viewing the content that is being provided to the participant.

## External data sharing

This study randomizes family clusters into one of four trial arms. Two of those trial arms involve increased personalized support from a FGHP Navigator based at Stanford University. For those participants randomized to receive this support, UM share study data with Stanford University so that the Navigator can effectively support the family. Data are shared externally with Stanford University via the Project Dashboard Console described above. Participants consent to all external data sharing and only minimum necessary, de-identified datasets are shared.

## Data retention and destruction

The merged analytic datasets will stay live through the end of the grant period. All PII will be destroyed at the end of study period and only a de-identified set of crosswalk variables will be retained for purposes of linking the FGHP trial datasets to the IMS patient inception cohort data. At that time, all data stored in the database will be exported to.csv files and de-identified final datasets will be provided to the analytic team. No data will be used for the purposes of publication or public presentations without express permission of the Leadership Team.

## Quality assurance

The Data Manager assesses the PIC survey data (the only survey that is made available in paper format per the study protocol) for the degree of missing values on an ongoing basis during the initial patient survey fieldwork. Otherwise, we anticipate minimal missing data from that collected online, based on the prior expertise of CHCR in conducting and collecting online data.

